#### Primary Analysis on Primary End Point

The primary efficacy end point is the percentage of achievement of a mean reduction of at least 10% of azoturia (grams per 24 h) or the achievement of a mean increase of at least 15% of distance (meters in the 6-MWT) or the achievement of a mean decrease of at least 10% of perceived stress (according to the PSS of Cohen) in KidneYou users exposed to a 3-month NP, PA program, and MP compared to KidneYou nonusers and not exposed to the same 3-month programs.

The observed percentages (in KidneYou users vs KidneYou nonusers) will be tested using a chi-square test or the Fisher exact test, as appropriate.

The secondary analyses on the primary end point include (1) achievement of each single component of the primary end point in each randomized group, (2) achievement of 2 or more of the aforementioned components of the primary end point, and (3) assessment of between-group differences in primary end point results by estimated eGFR category of patients with CKD (eg, G3b and G4) and by albuminuria category of patients with CKD (eg, A1, A2, and A3).

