### Study Design

This is a multicenter, randomized, 2-arm, comparative, parallel, open-label, premarket study on individuals affected by CKD belonging to GFR categories G3b or G4, and with persistent albuminuria categories A1, A2, or A3 (A3 limited to >300 mg/g [>30 mg/mmol] and <3000 mg/g [<300 mg/mmol]).

This study is a premarket clinical investigation conducted in accordance with European Union Medical Device Regulation n.2017/745 requirements, with the goal of generating clinical evidence necessary for Conformité Européenne marking of the investigational medical device.

Enrolled participants are randomly allocated in a ratio of 1:1 to one of the two treatment arms using a randomization list that is computer generated by the trial statistician and provided through a web-based approach (via interactive response technology or randomization and trial supply management): group A (KidneYou users; investigational arm) or group B (KidneYou nonusers; control arm). A randomization list with random permuted blocks of different sizes (2 or 4 or 6 or 8) has been prepared and included in the electronic case report form (eCRF).

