### Assessments

Each participant undergoes 4 visits and is examined according to the following schedule: baseline (V0), 6-week visit (V1), 12-week visit (V2), and 4-week follow-up visit (V3). During the baseline visit, the patient signs the informed consent form and is evaluated for inclusion and exclusion criteria. Once enrollment is confirmed, the patient is randomized. The PSS questionnaire is administered to all enrolled patients, regardless of the randomization group. At V0, V1, V2, and V3, a complete physical examination is performed; vital signs (systolic blood pressure, diastolic blood pressure, HR, and respiratory rate), ongoing medications for CKD, and concomitant medications are collected.

At V0, V2, and V3, laboratory tests are also performed and include hematology (complete blood count, glycemia, proteins [albumin], and creatinine), minerals (phosphorus and calcium), electrolytes (sodium, potassium, chloride, and bicarbonate), azotemia, and uric acid; lipid profile, that is, total cholesterol, high-density lipoprotein cholesterol, low-density lipoprotein cholesterol, and triglycerides; and urine tests (24 h urinary excretion collection), that is, urea nitrogen, uric acid, minerals (phosphorus and calcium), electrolytes (potassium, sodium, chloride, and bicarbonate), albumin, creatinine, glucose, density, pH, proteins, ketones, hemoglobin, bilirubin, nitrites, white cells, red blood cells, casts, crystals, epithelial cells, and serum pregnancy test, only for women of childbearing potential.

All patients undergo the 6-MWT and bioimpedance test. Safety, including the appearance of adverse device effects and abnormalities in physical and laboratory parameters, is assessed throughout the entire study period.

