### Statistics

#### Sample Size Calculation

This study is designed to test the null hypothesis that the percentage *success* (defined by the achievement of at least one of the 3 conditions described in the primary end point, with no hierarchical structure among them) in KidneYou nonusers is equal to the percentage “success” in KidneYou users. The alternative hypothesis is that the percentage “success” in KidneYou nonusers is different from the percentage “success” in KidneYou users.

The sample size is estimated to assess the study hypothesis on the primary end point.

The sample size calculation is based on the combination of the expected proportion of success in the control group and the expected delta (Δ) of success in the experimental group.

With a significance level α equal to .05 and a power equal to 80%, a sample size of 190 participants (95 per group) is required to detect as significant, if any, a success delta in favor of the experimental group equal to 20% (under the hypothesis of success rate of 40% in the control group and success rate of 60% in the experimental group). Considering a dropout rate of approximately 10%, a total of 210 patients (105 per group) will have to be enrolled. A competitive enrollment approach across the centers involved in the study will be used to reach the sample size efficiently.

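### The unadjusted primary test is valid, but a standardised analysis adjusted for baseline azoturia, walk distance and PSS could add a little precision, about 0 to 2 points of power

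*Protocol article*

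**What the plan says.** Under Primary Analysis on Primary End Point, the article fixes the confirmatory test: "The observed percentages (in KidneYou users vs KidneYou nonusers) will be tested using a chi-square test or the Fisher exact test, as appropriate". It mentions no covariate. Mixed models appear only under the statistical section for secondary end points, as something to be considered.

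The Study Design section describes a 1:1 list with "random permuted blocks of different sizes (2 or 4 or 6 or 8") and names no stratification factor.

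The baselines should be on file:
- **Azoturia:** the Assessments section says "At V0, V2, and V3, laboratory tests are also performed", and these include 24-hour urinary urea nitrogen.
- **PSS:** it is an entry criterion (total score above 12) and is listed at V0 among the secondary end points.
- **6-minute walk:** all patients do it. The visits are not listed under Assessments, but a 15% increase cannot be computed without a V0 value.

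The Sample Size Calculation section sizes the trial for the same crude comparison, "under the hypothesis of success rate of 40% in the control group and success rate of 60% in the experimental group".

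**The concern.** A patient succeeds by crossing a percent-change threshold on at least one of three measures. I read this as the patient's own change from V0, which is the reading that makes a percentage of successes computable. The V0 value is then the denominator of each change. Unless the later value tracks it almost perfectly, a patient with a high V0 azoturia or PSS, or a short V0 walk, is more likely to cross the threshold through regression to the mean alone.

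If so, the baselines explain part of the variation in success, and a comparison that uses them is more precise at no cost in data. At stake is a small amount of power, and an estimate less affected by whatever baseline imbalance happens to arise. The planned test has little slack at its evaluable sample size, so even a small gain has some value.

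**Working it through.** **1. Inputs from the article.** "With a significance level α equal to .05 and a power equal to 80"%; 40% versus 60%; "a sample size of 190 participants (95 per group) is required to detect as significant"; "Considering a dropout rate of approximately 10%, a total of 210 patients (105 per group) will have to be enrolled". I take the test as two-sided, because the alternative hypothesis is that the percentages differ.

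**2. The plan's own figure.** Unpooled formula, n per arm = (1.960 + 0.842)² × (0.4×0.6 + 0.6×0.4) / 0.2² = 7.849 × 0.48 / 0.04 = 94.2, so 95 per arm and 190 in all. The stated figure is reproduced.

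**3. Power of the planned chi-square.** The chi-square uses the pooled variance under the null: power = Φ[(Δ√n − 1.960√(2p̄q̄)) / √(p₁q₁ + p₂q₂)]. At n = 95 this is Φ[(1.949 − 1.386) / 0.693] = Φ(0.813) = 79.2%. At 105 per arm it is 83.1%.

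**4. What adjustment could add, by formula.** If the baselines explain a share R² of the variance of success, the effective n is 95/(1 − R²):

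| R² | Power |
|---|---|
| 0% | 79.2% |
| 2% | 80.0% |
| 5% | 81.2% |
| 10% | 83.3% |

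The article gives no R², so a plausible range has to come from assumptions.

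**5. Simulation at the planned rates.** 4,000 trials per row; 95 per arm; any-of-three composite calibrated to 40% versus 60%. Assumed between-patient CVs are 30% (azoturia), 20% (walk) and 25% (PSS). ρ is the assumed correlation between V0 and week 12. The adjusted analysis is a logistic model on arm and the three baselines, standardised to a risk difference, with an influence-function standard error. The PSS entry cut was not imposed. It narrows the baseline range and would probably weaken the link.

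| ρ | Chi-square power | Adjusted power | Variance ratio, crude/adjusted | Variance cut (1 − 1/ratio) |
|---|---|---|---|---|
| 0.5 | 79.4% | 82.4% | 1.067 | 6% |
| 0.7 | 78.6% | 80.3% | 1.034 | 3% |
| 0.8 | 78.9% | 80.1% | 1.006 | 1% |
| 0.9 | 79.3% | 79.6% | 0.999 | 0% |

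With no true effect, the chi-square rejected 4.8 to 5.3% of the time and the adjusted test 5.4 to 6.1%. The Monte Carlo standard error is √(0.05×0.95/4000) = 0.34 points. The top value of 6.1% is therefore about three standard errors above 5%.

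**6. How much of the gain is precision.** Putting the variance ratios into the step 3 formula (n = 95 × ratio) gives 81.7%, 80.5%, 79.5% and 79.2%. These are gains of 2.5, 1.3, 0.3 and 0 points, less than the observed 3.0, 1.7, 1.2 and 0.3. One reason is visible in steps 2 and 3. A Wald test with unpooled variance (0.48 rather than 0.50) has power Φ(0.2/√(0.48/95) − 1.960) = 80.3% with no covariates, which is 1.1 points above the chi-square.

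Scenarios at higher success rates show the same pattern:
- 63% versus 79%: variance ratio (adjusted/crude) 0.967, power 70.2% to 73.0%. Precision alone gives Φ(2.490/√0.967 − 1.960) = 71.6%.
- 70% versus 86%: variance ratio 0.974, power 74.2% to 77.1%. Precision alone gives Φ(2.609/√0.974 − 1.960) = 75.3%.

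**7. With a corrected standard error.** A further simulation at 40% versus 60%, 95 per arm, gave variance ratios (adjusted/crude) of 0.96 to 1.01. With a degrees-of-freedom-corrected standard error the gains were about 2 points at ρ = 0.5, 1 point at 0.7 to 0.8, and none at 0.9. The uncorrected large-sample standard error rejected 5.5 to 6.4% of nulls. As a cross-check, a 4% variance cut gives an effective n of 95/0.96 = 99.0 and power of 80.8%, a gain of 1.6 points.

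**The case against.** The strongest reply is that nothing here is wrong. The hypothesis is equality of two percentages, the trial is sized for that comparison, and the chi-square tests it. No stratification factor is named, so none is left out of the analysis. An adjusted analysis may already sit in a statistical analysis plan that is not shown. All of this stands.

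Four stronger readings are tempting, and the document does not support them:
- **That the crude test is biased or unprotected against chance imbalance.** Randomisation is the protection, and the 5% error rate already allows for imbalance. Adjustment improves precision and does not repair validity.
- **That the baselines are known to predict success.** The article reports no such association. The any-of-three composite and the PSS entry cut both tend to dilute it.
- **That the power is free.** A large-sample standard error can reject too often at 190 patients, so a correction is needed, as are a fixed model and a rule for missing baselines.
- **That the primary test should be replaced whatever the stage.** The trial is open-label, recruitment ended in April 2024, and the Results section says analysis is ongoing. The article does not show whether results by arm have been seen. If they have, changing the single confirmatory test would be post hoc.

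What survives is the efficiency point: the article commits the confirmatory test to an unadjusted form although useful baselines are at hand.

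**Conclusion.** The point holds as an optional, low-severity improvement in efficiency. The planned test is valid and consistent with the sample size. Adjustment for the three baselines would cut the variance of the risk difference by about 0 to 4% and add about 0 to 2 points of power with a corrected standard error. The most favourable run, at ρ = 0.5, reached a 6% cut, and at ρ = 0.9 there was no gain. These figures rest on the assumed CVs and correlations and on a patient-level reading of success. The direction of the association follows from how the end point is built; its strength is not given in the article.

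**What to change.** **If no results by arm have been seen,** document as primary a standardised (marginal) risk difference from a logistic model of composite success on arm, V0 azoturia, V0 6-minute walk distance and V0 PSS. eGFR category (G3b or G4) may be added, but the simulations above did not include it. State in the same dated text:
- the variance estimator, with a small-sample correction, or a randomisation test instead;
- how missing baseline values are handled;
- that the chi-square or Fisher test is kept as supportive.

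**If results by arm have been seen,** keep the chi-square or Fisher test as primary and report the adjusted risk difference as supportive, with the date on which it was specified.

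The cost is a little programming, a variance correction and a short documented amendment. No further data are needed, and the estimand, the difference in success percentages, is unchanged.

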#### Primary End Point

The primary end point is as follows: (1) to evaluate the achievement of a mean reduction of at least 10% of azoturia (gram per 24 h) in CKD KidneYou users exposed to a 3-month NP compared to CKD KidneYou nonusers exposed to the same 3-month NP, (2) to evaluate the achievement of a mean increase of at least 15% of the distance (meters in the 6-MWT) in CKD KidneYou users exposed to a 3-month PA program compared to CKD KidneYou nonusers exposed to the same 3-month PA program, or (3) to evaluate the achievement of a mean decrease of at least 10% of perceived stress (according to the PSS of Cohen) in CKD KidneYou users exposed to a 3-month MP compared to CKD KidneYou nonusers and not exposed to the same MP.

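### The any-of-three success test discards the size of change and does not show which domain improved; the planned full-scale comparisons should become a named, baseline-adjusted, Holm-controlled supportive set that includes 6-MWT distance

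*Protocol article*

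**What the plan says.** Under Sample Size Calculation, success is "defined by the achievement of at least one of the 3 conditions described in the primary end point, with no hierarchical structure among them". The conditions are a fall of at least 10% in azoturia, a rise of at least 15% in 6-MWT distance, and a fall of at least 10% in PSS. Under Primary Analysis on Primary End Point, the confirmatory test is: "The observed percentages (in KidneYou users vs KidneYou nonusers) will be tested using a chi-square test or the Fisher exact test, as appropriate".

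The trial is sized on "success rate of 40% in the control group and success rate of 60% in the experimental group". On that basis "a sample size of 190 participants (95 per group) is required", and then "Considering a dropout rate of approximately 10%, a total of 210 patients (105 per group) will have to be enrolled".

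The primary analysis section adds secondary looks at each single component and at two or more components. The Secondary End Points list has between-group differences in mean change for azoturia and PSS. For the 6-MWT it lists only heart rate, blood pressure and oxygen saturation. The statistical text for secondary end points uses unpaired t or Wilcoxon-Mann-Whitney tests between groups and says that repeated-measures mixed models will be considered.

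**The concern.** All three inputs are measured on a full scale (grams per 24 h, metres, total score), but the confirmatory test sees only which side of a cut a patient falls on. Take an eligible patient with a baseline PSS of 20 (an illustrative value; entry needs more than 12). The 10% cut is then 2 points. A 2-point fall and a 10-point fall both count as success, while a 1-point fall counts the same as a rise. Meeting one condition counts the same as meeting three.

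The second issue is interpretation. The Primary Objective lists diet, energy expenditure and stress as separate aims joined by 'or'. Under Treatment Arms, controls receive the nutritional and activity programs on paper but no guidance on stress reduction. A significant chi-square could therefore come from PSS alone, with no gain in diet or walking. For a premarket study meant to support CE marking, readers will want to know which domain moved and by how much.

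**Working it through.** **Inputs.** From Sample Size Calculation: alpha .05, power 80%, success 40% v 60%, 95 per group, about 10% dropout, 210 enrolled. Two-sided testing is inferred from an alternative worded as a difference. Allocation is 1:1 (Study Design). The article gives no SD, component success rate or correlation, so steps 2 and 3 rest on assumptions.

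**1. The plan's own figure.**
- Unpooled formula: n = (1.960 + 0.842)² × (0.24 + 0.24) / 0.20² = 94.2, so 95 per group. The pooled version gives 97.
- Chi-square power at 95: z = (0.20√95 − 1.960√0.50) / √0.48 = (1.949 − 1.386) / 0.693 = 0.813, so 79.2%. Exact enumeration gives 79.3%. Fisher's exact test gives 74.8%.
- If all 105 per group are evaluable: 83.1% (exact 82.1%).
- Dropout: 190/0.9 = 211 and 190 × 1.1 = 209, so 210 is in tolerance.

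**2. Full-scale tests under a general shift.** Assume three independent normal changes with equal component rates, calibrated to 40% v 60%.
- Control rate per component: 1 − 0.60^(1/3) = 0.157, so the cut lies 1.009 SD above the control mean.
- App rate per component: 1 − 0.40^(1/3) = 0.263, so the cut lies 0.634 SD above the app mean. The shift is 1.009 − 0.634 = 0.375 SD.
- Standardised difference: 0.375 / √(2/95) = 2.585. The critical value at two-sided 0.05/3, Holm's first step, is 2.394.
- Power per component: Φ(2.585 − 2.394) = 0.576. At least one of three: 1 − 0.424³ = 0.924.

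**3. Full-scale tests when only a fraction responds.** Let a fraction q of app patients shift by 1.5 SD on a component.
- q = (0.263 − 0.157) / (Φ(1.5 − 1.009) − 0.157) = 0.107 / 0.532 = 0.200.
- Mean shift 0.301 SD; app-arm variance 1 + 0.20 × 0.80 × 1.5² = 1.36; SE = √((1 + 1.36)/95) = 0.158.
- Power per component: Φ(0.301/0.158 − 2.394) = 0.313. At least one of three: 1 − 0.687³ = 0.68.

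**4. Range over the models examined.** All are calibrated to about 40% v 60% success, so chi-square power stays near 79% (78% to 81% where simulated).

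| Effect model | At least one full-scale test significant at 0.05/3 |
|---|---|
| General normal shift, correlation 0 to 0.9, equal or unequal effects | 90.5% to 100% |
| General shift, heavy tails (t, 3 to 8 df), t tests | 71% to 90% |
| The same, Wilcoxon tests | 91.5% to 94% |
| Only a fraction responds (shift 0.5 to 3 SD) | 68% to 89% |
| Different patients respond in different domains (simulation) | 54% to 68% |
| One third of non-successes converted on one measure, no general shift (simulation) | 11% to 61% |

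**5. 6-MWT distance.** Secondary Objectives include between-group differences in physical function improvement. The Secondary End Points that should serve this objective list heart rate, blood pressure and oxygen saturation during the walk, not distance. Of the three primary components, distance alone has no full-scale between-group end point listed.

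**6. Adjustment.** With equal variance at both visits and V0-to-V2 correlation ρ, an unadjusted comparison of change has variance proportional to 2(1 − ρ), and a V0-adjusted one to 1 − ρ². The ratio is (1 + ρ)/2, which is below 1 for any ρ below 1. The article does not give ρ, so the gain cannot be sized.

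**The case against.** The strongest reply is that the success percentage is a legitimate target in its own right. The app is tailored to the individual across three domains, and an any-of-three rule is built to capture different patients improving in different ways. In that setting the full-scale tests lose power, as the lower rows of the table show. Nothing in the article makes a uniform shift more likely. This stands, and it rules out replacing the primary test on grounds of power.

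The power figures also do not transfer directly to the supportive set. The cuts are percentage changes from baseline, while the comparisons suggested below use absolute change adjusted for V0. This too stands.

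The article already plans component-level analyses and mean comparisons for azoturia and PSS, so the domain question is not ignored. Its silence on the reason for the cuts and on multiplicity may be filled by the full plan or SAP, and neither silence is counted against it here. What remains is that the article specifies unadjusted tests, only considers models, and lists no full-scale comparison for distance.

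Finally, recruitment is complete and analysis is under way in an open-label premarket trial sized on the success hypothesis. Changing the confirmatory end point now would cost credibility.

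**Conclusion.** The point holds as an improvement to the supportive analyses, not as an error in the primary one. The primary test discards the size of change, and alone it does not identify the domain that improved.

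A reader might infer two stronger things. One is that the trial is underpowered: 79% at 95 per group agrees with the stated 80% within tolerance, and power is 82% to 83% if all 210 are evaluable. The other is that full-scale testing would give 92% or more and should take over as primary. The 92% is the result of an assumed uniform normal shift with independent components. Full-scale power is about 91% or more for general shifts, with rank tests where tails are heavy. It is about 11% to 89% when only some patients respond or different patients respond in different domains, against about 79% for the success test. The documents do not say which case applies.

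**What to change.** Keep the chi-square on the success percentage as the primary test, and report the risk difference with its 95% CI.

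Name as the first supportive analysis three between-arm comparisons of V0-to-V2 change: azoturia in g/24 h, 6-MWT distance in metres and PSS total. Adjust each for its own V0 value and apply Holm across the three at two-sided 5%. This replaces, for these measures, the unadjusted between-group tests under Secondary End Points. Provide a rank-based version for heavy-tailed changes. Add 6-MWT distance to the secondary end points so that the physical function objective has a matching measure.

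The cost is a little more analysis work and a dated amendment; no new patients, visits or data are needed. The amendment must precede sight of the arm comparison. If that comparison has already been seen, label the set post hoc.

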## Results

Data will be analyzed and presented following the guidelines outlined in the international CONSORT to ensure the integrity and transparency of the results. The primary and secondary end points will be rigorously examined to assess the effectiveness of the KidneYou app in promoting adherence to nonpharmacological interventions (such as NP, PA program, and MPs) and improving health outcomes in patients with CKD.

Recruitment began in July 2022 and was completed in April 2024 across 12 Italian nephrology centers with a total number of 210 participants enrolled. Data analysis is currently ongoing. The results are expected to be published by early 2026.

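### Results by eGFR and albuminuria category are planned without any listed test that compares the treatment effect across categories; separate tests would often suggest a false difference

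*Protocol article*

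**What the plan says.** Under Secondary Objectives, the protocol article sets out to break the primary results down by GFR category (G3b, G4) and by albuminuria category (A1, A2, A3). Under Secondary End Points (in Main Objectives and End Points), this becomes a stratification of both within-group changes and between-group differences, for each of the two factors. Under Primary Analysis on Primary End Point, the between-group part returns as a secondary analysis of the composite: "assessment of between-group differences in primary end point results by estimated eGFR category of patients with CKD (eg, G3b and G4"), with albuminuria category named alongside.

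The methods named are these:

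- For the composite, the observed percentages in users and nonusers "will be tested using a chi-square test or the Fisher exact test, as appropriate".
- For secondary end points (Statistics), between-group comparisons use unpaired t, Wilcoxon-Mann-Whitney, chi-square or Fisher tests. Within-group comparisons use paired t tests, a nonparametric alternative or McNemar.
- Mixed linear models for repeated measures are to be considered as well. No arm-by-category term is mentioned.

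No interaction or heterogeneity test is named, and no rule is given for interpreting the category results.

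**The concern.** Breaking a result down by CKD stage invites the question whether the app works differently in G3b and G4, or across A1 to A3. A between-arm test inside one category asks only whether there is an effect there. A within-arm before-after test asks less still, because it makes no comparison with control. Neither addresses whether the effect differs between categories.

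The trial is sized for one overall comparison, so each category has much less than 80% power. When two or three underpowered tests are set side by side, some come out significant and others do not, even if the true effect is identical. A reader may take that pattern as a difference by CKD stage. The study is meant to support Conformité Européenne marking (Study Design), so a spurious statement about which patients benefit could affect how the device is described.

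**Working it through.** **Inputs from the protocol article.** Planning rates: "under the hypothesis of success rate of 40% in the control group and success rate of 60% in the experimental group". Size: "With a significance level α equal to .05 and a power equal to 80%, a sample size of 190 participants (95 per group) is required". The test is two-sided: "The alternative hypothesis is that the percentage “success” in KidneYou nonusers is different from the percentage “success” in KidneYou users". Allocation: "Enrolled participants are randomly allocated in a ratio of 1:1 to one of the two treatment arms". Enrolment: "Considering a dropout rate of approximately 10%, a total of 210 patients (105 per group) will have to be enrolled", and the Results section reports the trial "with a total number of 210 participants enrolled".

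**Assumed, because the article gives no category sizes.** G3b/G4 splits from 50:50 to 80:20; equal thirds for A1/A2/A3, with unequal splits as a check. Analysed numbers of 95 per arm (planned evaluable) and 105 per arm (all enrolled). The same true 40% v 60% in every category.

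**Step 1: the plan's own figure.** With unpooled variance, n per arm = (1.96 + 0.8416)² × (0.4×0.6 + 0.6×0.4) / 0.20² = 7.849 × 0.48 / 0.04 = 94.2, so 95 per arm and 190 in total. This matches. Adding 10% gives 190 × 1.10 = 209, about 210.

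**Step 2: power inside one eGFR category.** With n per arm in the category,

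power = Φ{[0.20 − 1.96 × √(2×0.25/n)] / √(0.48/n)}.

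The two categories contain different patients, so P(exactly one significant) = p₁(1 − p₂) + p₂(1 − p₁).

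| Per arm | Split | Power, larger / smaller category | Exactly one significant |
|---|---|---|---|
| 95 | 50:50 | 0.496 / 0.496 | 50% |
| 95 | 60:40 | 0.571 / 0.413 | 51% |
| 95 | 70:30 | 0.638 / 0.323 | 55% |
| 95 | 80:20 | 0.697 / 0.229 | 61% |
| 105 | 50:50 | 0.536 / 0.536 | 50% |
| 105 | 60:40 | 0.614 / 0.448 | 51% |
| 105 | 70:30 | 0.682 / 0.352 | 55% |
| 105 | 80:20 | 0.741 / 0.249 | 62% |

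Exact binomial power of the uncorrected chi-square test, with whole-number category sizes, gives almost the same results. For 105 per arm, a split of 52 and 53 gives powers of 0.574 and 0.519 and 50% discordance. A split of 84 and 21 gives 0.752 and 0.242, and 63% discordance. The range is therefore about 50% to 63%.

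**Step 3: three albuminuria categories.** With equal thirds of 105 (35 per arm), exact power is 0.365. P(mixed) = 1 − 0.365³ − 0.635³ = 1 − 0.049 − 0.256 = 0.70. The normal approximation gives 0.69 (95 per arm) and 0.71 (105 per arm). Unequal splits up to 60:30:10 give 0.70 to 0.76.

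**Step 4: what an interaction test does under the same uniform effect.** In 200,000 simulated trials per setting, a Wald test of the difference in risk difference between two eGFR categories was significant in 5.3% to 5.6%. Among trials where exactly one category was significant, only about 9% to 11% also had a significant interaction.

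**Step 5: how much an interaction test can detect.** For a true effect of 20 points in one category and none in the other, 95 per arm split 50:50:

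SE = √(0.48/47.5 + 0.48/47.5) = 0.142; 0.20/0.142 = 1.41; power = Φ(1.41 − 1.96) ≈ 0.29.

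Across splits of 50:50 to 70:30 and 95 to 105 per arm, power is about 25% to 32% for a 20-point difference in effect and about 75% to 87% for a 40-point difference. Under a uniform effect with equal categories, the 95% CI half-width for the difference in risk difference is 1.96 × √(2×0.48/52.5) = 0.27 at 105 per arm and 1.96 × √(2×0.48/47.5) = 0.28 at 95. Either is wider than the whole planned effect of 20 points.

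These figures concern between-arm tests on composite success. The within-group comparisons are not quantified; the objection to them is the logical one given above.

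**The case against.** The strongest defence is that the article never says category results will be read by setting p values side by side. A reader might infer that the sponsor plans to claim a difference by CKD stage whenever one category is significant and another is not. The text does not support that: it states no hypothesis of differential effect and no decision rule. This stands, and the point is limited to what the listed tests can and cannot show.

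A second defence is that the article condenses a fuller plan, and an unseen analysis plan may contain an interaction term. That is possible. However, the article goes beyond silence: it commits to the category comparisons and lists tests, and those tests cannot answer the question the breakdown raises.

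Third, the chi-square/Fisher sentence is written for the overall comparison, and the category item names no test of its own. Applying those tests within categories is a natural reading, since the stratified results are secondary end points and the general list for secondary end points includes them. It is still a reading. The repeated-measures model is not excluded, but it is optional and no arm-by-category term is named.

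Fourth, an interaction test is weak at this size. That is true, and it is a reason to report estimates with intervals and to warn against reading non-significance as uniformity. It does not make separate tests a valid substitute.

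**Conclusion.** The concern holds in limited form. The article plans within-group and between-group results by eGFR and albuminuria category, and names no method that compares the treatment effect across categories. If the categories were tested separately, a uniform 40% v 60% effect would make exactly one of G3b and G4 significant in about 50% to 63% of trials, and would give a mixed picture across three equal albuminuria categories in about 70%. An interaction test would raise a false signal between G3b and G4 in about 5%.

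These sizes rest on the plan's own success rates, on category shares that the article does not give, and on category-level testing by chi-square. Only secondary analyses are affected, so the change is advisable but does not bear on the trial's main conclusion.

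**What to change.** For each factor, fit one model of composite success on arm, category and arm-by-category, with albuminuria as a three-level term. Report the interaction estimate with its confidence interval and p value, and category-specific risk differences with confidence intervals. Label these analyses exploratory. State that no difference by category will be inferred from separate between-group or within-group p values. State also that interaction power is low (about 25% to 32% for a 20-point difference in effect between G3b and G4), so a non-significant interaction is not evidence of a uniform effect.

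The cost is one model per factor and a revised table; no new data are needed. Because the article reports that analysis is already under way in an open-label trial, record the change as a dated addition to the analysis plan. If the full analysis plan already contains such a term, it is enough to say so when reporting.
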